### Secondary endpoint

The secondary endpoint focuses on evaluation of hepatic steatosis and its changes in obese individuals before and after bariatric surgery using QUS techniques (TAI, TSI) over a period of 1, 3, 6, and 12 months. Interpretation of the data collected will depend on whether significant differences are observed in QUS parameters pre- and post-surgery. The confirmation of such differences would furtherly signify the feasibility of using QUS techniques for postoperative evaluation of bariatric surgery. In addition, the trend in the changes of hepatic steatosis would evaluate the influence of bariatric surgery on obese individuals.

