## Introduction

Obesity has emerged as a chronic health condition that has garnered significant attention from the international community. The World Health Organization's latest report indicates a staggering prevalence of over 1.9 billion overweight adults globally, with over 650 million individuals classified as obese. The gravity of this epidemic demands immediate and sustained action to mitigate the social, economic, and health consequences associated with obesity (1). Obesity is associated with numerous comorbidities, such as metabolism-associated fatty liver disease (MAFLD), cardiovascular diseases, type 2 diabetes, hypertension, and dyslipidemia. Hepatic steatosis is commonly associated with obesity, and its prevalence can be as high as 80% in extremely obese individuals (2). In a study with 1,000 morbidly obese patients, more than 95% had MAFLD (3). The contribution of obesity and chronic low-grade systemic inflammation to the progression from hepatic steatosis to fibrosis is a matter of considerable significance. These factors are known to exert significant influence on the development of liver disease, thus warranting further scrutiny in this context (4). The recalcitrance of obesity portends a surge in the incidence of MAFLD, and as this cohort advances in age, a considerable proportion will encounter hepatic cirrhosis and end-stage liver maladies.

Severe obesity presents as a chronic condition that is resistant to treatment. While it is commonly believed that a combination of dietary adjustments and heightened physical exertion may yield considerable long-term advantages, such efforts prove challenging to uphold. Regrettably, over 95% of patients who attempt conservative interventions fail to attain desired outcomes. Bariatric surgery may be more effective than medical and lifestyle interventions for the most severe form of obesity to have major and sustainable weight loss, with RYGB being the most popular surgical procedure (5). Patients undergoing this surgery not only lose a substantial amount of weight, but also are clearly improved in clusters of the metabolic syndrome.

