The widespread employment of BMI as a metric for assessing the postoperative efficacy of clinical bariatric surgery is an established practice. However, this measure fails to discriminate between subcutaneous adipose tissue and visceral fat as well as muscle mass (6). The changes of laboratory values (like ALT, AST, HDL-c and LDL-c) after surgery are also the point of assessment of surgical effect (7), but lack of standardization. While liver biopsy remains the gold standard for diagnosing and grading hepatic steatosis, its invasiveness, lack of reproducibility, and potential complications preclude its use in ongoing monitoring efforts. The accurate grading of hepatic steatosis is crucial for the appropriate management of patients. While MRI-PDFF estimation offers a noninvasive alternative to liver biopsy, its high cost and limited availability constrain its global implementation (8–10). As an alternate noninvasive option, ultrasound (US) holds promise due to its widespread access and cost-effectiveness. B-mode US imaging based on the amplitude of the envelope of beamformed radiofrequency signals is routinely employed in clinics but suffers from operator-dependency, subjectivity, and low sensitivity to mild steatosis (11). While conventional US shows sensitivity and specificity ranges of 60%–94% and 66%–95%, respectively, it does not offer an adequate diagnostic tool for quantifying hepatic steatosis. Nonetheless, recent efforts have been made to develop QUS, which has the potential to enhance diagnostic accuracy and enable liver fat quantification (12, 13). QUS represents a promising application of this modality that may improve the diagnosis and management of hepatic steatosis.

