### Data analysis

The statistical analysis for this study will be performed using the SAS 9.2 software package (SAS Analytics, Marlow, UK) and R (v4.3.1; R Core Team), which is widely available for commercial use. The significance level has been predetermined to be 0.05 for all two-sided tests. The mean and standard deviation will be used to express normally distributed quantitative data.

To compare quantitative data, a paired t-test will be employed. Meanwhile, categorical variables will be analyzed using the chi-squared test. Pearson correlation coefficients will be utilized to evaluate the relationship between QUS parameters and other factors under consideration. Univariable linear regressions of QUS and other methods on MRI-PDFF were conducted to calculate the adjusted linear correlation coefficient (r). Then receiver operating characteristic (ROC) curves of QUS and other methods for the detection of MRI-PDFF ≥5% and ≥10% were plotted. The best cut-off values were defined as the cut-off values corresponding to the maximum Youden indexes.

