Pereira et al. (34) conducted a comparison of noninvasive biochemical methods and FibroScan with histopathologic analysis to evaluate hepatic fibrosis in patients who underwent bariatric surgery one year prior. The results indicate that noninvasive liver fibrosis evaluation correlates highly with liver biopsy findings after one year of bariatric surgery. While QUS techniques (TAI, TSI) are more advanced ultrasound technologies, they can theoretically assess the degree of hepatic steatosis accurately after bariatric surgery. In our pre-experiment study, we preliminarily verified the feasibility of the QUS techniques in Chinese participants who suspected NAFLD. The results of the pre-experiment signified the feasibility of using QUS techniques for postoperative evaluation of bariatric surgery, making our study design reasonable.

Our study inevitably has some limitations. Specifically, we utilized MRI-PDFF rather than biopsy as the gold standard to correlate QUS parameters. Although previous research suggests that MRI-PDFF exhibits relatively high sensitivity and specificity in detecting fatty liver disease, there remains potential for incorrect diagnoses. In addition, although we conducted health education for participants before surgery, it was difficult to avoid that confounding factors (like life-style) may influence on results. Furthermore, confounding factors such as increased subcutaneous fat in individuals with higher BMI may influence QUS parameter results. With a larger patient population, we will summarize the imaging experience in hepatic steatosis evaluation by QUS techniques in obese people. We will also analyze the influence of scanning methods, imaging location and other influencing factors on the results, and explore how to improve the results.

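### A significant pre/post change in QUS, the secondary endpoint's sign of feasibility, cannot separate tracking of liver fat from a body-wall effect of weight loss

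*Protocol article*

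**What the plan says.** The Secondary endpoint section sets the criterion, "Interpretation of the data collected will depend on whether significant differences are observed in QUS parameters pre- and post-surgery", and then the conclusion drawn from it: "The confirmation of such differences would furtherly signify the feasibility of using QUS techniques for postoperative evaluation of bariatric surgery". It names no reference standard, direction of change or allowance for body-wall fat.

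The Data analysis section gives the test, "To compare quantitative data, a paired t-test will be employed", and the level, "The significance level has been predetermined to be 0.05 for all two-sided tests". It also plans Pearson correlations of QUS with other factors, univariable regressions of QUS and the other methods on MRI-PDFF, and ROC curves against MRI-PDFF thresholds of 5% and 10%. It does not say that any of these uses within-patient changes.

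Three other statements bear on the point:
- Introduction, on the operation: "Patients undergoing this surgery not only lose a substantial amount of weight".
- Introduction, on BMI as an outcome measure: "this measure fails to discriminate between subcutaneous adipose tissue and visceral fat as well as muscle mass".
- Discussion, limitations: "confounding factors such as increased subcutaneous fat in individuals with higher BMI may influence QUS parameter results".

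Under the Intervention heading of the Design section, MRI-PDFF, QUS and BMI are all scheduled before surgery and at 1, 3, 6 and 12 months.

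**The concern.** A pre/post difference shows that a reading responds to surgery and to everything that changes with surgery. It does not show which change the reading follows. Here the confounder that the authors name moves systematically between the two time points compared: patients lose weight, and the Discussion cites studies in which steatosis regressed as weight fell. A QUS parameter that responds only to the thickness of the body wall would shift in the same period as one that follows liver fat.

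BMI shows how little the criterion discriminates. The Introduction faults BMI because it cannot tell fat compartments apart, yet BMI would meet the same criterion after bariatric surgery. The rule therefore cannot distinguish QUS from a measure it is meant to improve on.

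At stake is the secondary statement that QUS can be used for follow-up after surgery. That use needs evidence that QUS moves with liver fat within a patient, which this criterion does not supply.

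**Working it through.** **The plan's own figure.** The plan gives no sample size or power for the secondary endpoint. The minimum of 75 patients (Sample size section) comes from assumed prevalence, sensitivity and specificity with no stated power, so it cannot be confirmed. Nothing here depends on it beyond using 75 as the number of pairs.

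**Inputs from the protocol.** Paired t-test, two-sided 0.05; 75 pairs.

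**Assumed inputs (the protocol gives none).**
- ρ, correlation of the QUS parameter with BMI: 0.2 to 0.3. The parameter has no dependence on liver fat.
- w, within-patient correlation of QUS between two visits: 0 to 0.7.
- k, fall in BMI in baseline SDs: 0.5, 1 or 2.
- The between-patient slope on BMI also applies within patients.

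**Formula.** With QUS in SD units, the mean change is ρk and the SD of the differences is √(2(1−w)). The standardised paired change is d = ρk / √(2(1−w)). The pass probability comes from the noncentral t distribution with 74 degrees of freedom and noncentrality d√75.

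Example: ρ = 0.3, k = 1, w = 0.5 gives d = 0.30/√1 = 0.30, noncentrality 0.30 × 8.66 = 2.60, probability 73%.

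**Probability that the uninformative parameter passes at one visit:**

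| BMI fall | ρ | w = 0 | w = 0.5 | w = 0.7 |
|---|---|---|---|---|
| 0.5 SD | 0.2 | 9% | 14% | 20% |
| 0.5 SD | 0.3 | 15% | 25% | 38% |
| 1 SD | 0.2 | 23% | 40% | 60% |
| 1 SD | 0.3 | 44% | 73% | 91% |
| 2 SD | 0.2 | 68% | 93% | 99% |
| 2 SD | 0.3 | 95% | >99% | >99% |

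**Second check, by simulation.** The QUS reading depended only on subcutaneous fat, with 4,000 runs per setting.
- Correlation 0.5, subcutaneous fat falling 1 SD: the paired t-test is passed in 91% of trials at 75 pairs and 97% at 100.
- Correlation 0.1, falls of 0.5 to 1.5 SD, 100 pairs: 6% to 19%.
- Testing the correlation of QUS change with MRI-PDFF change instead, the same reading passes in 4.4% to 5.7% of trials across all settings. Here the changes in subcutaneous and liver fat were independent between patients. If they are correlated, adjustment for body-size change is also needed.

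**Form of the replacement model.** In simulation, a mixed model of QUS on within-patient MRI-PDFF, adjusted for BMI change but without visit, still declared an uninformative parameter associated with MRI-PDFF in 8% to 76% of trials, depending on the assumed inputs. The shared postoperative fall drives the slope, and BMI is an imperfect proxy for subcutaneous fat. Adding visit as a factor, or correlating the 12-month changes, returned about 5%.

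**The case against.** The strongest reply is that the secondary endpoint does not stand alone. Its wording presents the result as further support, beside a primary endpoint that takes MRI-PDFF as gold standard before and after surgery and requires QUS to do better than anthropometric and other measures. A reading that tracked only subcutaneous fat should struggle there. This stands in part. A reader might infer that the protocol treats the pre/post change as proof, or that the trial could declare feasibility with no reference to liver fat. The documents support neither. But the primary comparison, as stated, concerns levels of QUS and MRI-PDFF, and agreement across patients does not establish tracking within a patient.

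A second reply is that the planned Pearson correlations could be run on changes, that the Discussion promises to examine influencing factors, and that model detail may sit in an analysis plan not shown. It is fair that nothing excludes a change-on-change analysis, so one cannot say it will never be done. But the inference from a pre/post difference to feasibility is written into the protocol itself.

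Third, the size depends on the assumptions. With weak contamination or a small BMI fall the pass probability is low. Nor is the comparison with 5% a type I error in the strict sense: QUS really does change in this scenario, and the error lies in the interpretation.

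A reader might also infer separate tests on whatever pairs are available, with 25% loss planned (1 − 75/100). The protocol states no dropout rate and does not describe the handling of missing pairs, so that forms no part of this point.

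**Conclusion.** The inference in the Secondary endpoint section is not valid as written. A significant pre/post difference in QUS is compatible both with tracking of liver fat and with a body-wall effect that the authors themselves acknowledge. For a parameter with no liver-fat information, the chance of meeting the criterion at one visit runs from about 9% to over 99% across the inputs examined. It is mostly high once BMI falls by 1 SD or more. Every correlation and fall used is an assumption, because the protocol gives none; the logical flaw does not depend on them.

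The scope is the secondary feasibility conclusion, not the trial as a whole. It should be fixed before analysis.

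**What to change.** In the Secondary endpoint and Data analysis sections, base the secondary feasibility conclusion on the association between within-patient change in QUS and within-patient change in MRI-PDFF:

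- For each QUS parameter, fit a linear mixed model over all five visits, with visit as a factor, a random patient effect, MRI-PDFF split into within-patient and between-patient parts, and adjustment for within-patient BMI change.
- Report the within-patient MRI-PDFF slope with its confidence interval, and the correlation of QUS change with MRI-PDFF change at 12 months.
- Keep the pre/post differences in QUS as a description of the effect of surgery, and remove the sentence that draws feasibility from them.

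Visit must be in the model, since BMI adjustment alone does not remove the shared postoperative fall. Because BMI is an imperfect proxy for subcutaneous fat, some body-wall confounding may remain and should be acknowledged.

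The cost is revised wording and modest programming on data already scheduled at every visit. The criterion is stricter, and QUS may fail it.

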### I (intervention)

All patients will receive anthropometric measurements (BMI, waist circumference, hip circumference), blood-based biochemical analyses (alanine aminotransferase ALT, aspertate aminotransferase AST, γ-glutamine transferase γ-GTP, total cholesterol Tc, triglyceride, high-density lipoprotein cholesterol HDL-c, low-density lipoprotein cholesterol LDL-c), ultrasonic examination (B-mode US, CAP, TAI, TSI) and magnetic resonance imaging proton density fat fraction (MRI-PDFF) before and 1, 3, 6, 12 months after bariatric surgery.

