### After inclusion

This study includes anthropometric measurements, blood-based biochemical analyses, ultrasonic examination and MRI-PDFF. All parts are completed independently in a blind state. There is no specific requirement on the sequence of the examinations. All examinations shall be conducted on the same day. All participants were educated after inclusion, and they were told to maintain a reasonable and stable lifestyle as much as possible after surgery, so as to avoid experimental error from unreasonable lifestyle (such as fasting, overeating).

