### Primary endpoint

In this study, the primary endpoint seeks to evaluate the efficacy of QUS techniques assessing hepatic steatosis, utilizing MRI-PDFF as the gold standard, compared to anthropometric measurements, laboratory assessments and other imaging methods before and after bariatric surgery. Success in this endeavor would be measured by the ability of QUS techniques to better evaluate the degree of hepatic steatosis as compared to other methods, thereby providing diagnostic improvement beyond current practice. Such results would signify the feasibility of using QUS techniques for postoperative evaluation of bariatric surgery.

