### Tertiary endpoint

Finally, the tertiary endpoint aims to observe the changes of indicators (anthropometry, laboratory assessment, imaging examination) before and after bariatric surgery, and compare the correlation between QUS and traditional evaluation indices. It may indicate whether there are differences in these indicators before and 1, 3, 6 and 12 months after bariatric surgery, and these differences will assess the influence of bariatric surgery on these indicators.

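### The secondary endpoint reads surgery's influence on liver fat from QUS, the test under evaluation, although the MRI-PDFF reference is measured at the same five visits

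*Protocol article*

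**What the plan says.** All references are to the protocol article.

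- **Secondary endpoint** (also in O, outcome or objective). The object is "evaluation of hepatic steatosis and its changes in obese individuals before and after bariatric surgery using QUS techniques (TAI, TSI" at 1, 3, 6 and 12 months. Two conclusions follow. On the test: "The confirmation of such differences would furtherly signify the feasibility of using QUS techniques for postoperative evaluation of bariatric surgery". On surgery: "the trend in the changes of hepatic steatosis would evaluate the influence of bariatric surgery on obese individuals". This last sentence names no instrument, but QUS is the only one the endpoint mentions.
- **Primary endpoint.** The task is to "evaluate the efficacy of QUS techniques assessing hepatic steatosis, utilizing MRI-PDFF as the gold standard", against the competing methods, before and after surgery. The MRI section likewise treats the averaged PDFF reading as the reference for liver fat.
- **I (intervention)** and **After inclusion.** The schedule includes "magnetic resonance imaging proton density fat fraction (MRI-PDFF) before and 1, 3, 6, 12 months after bariatric surgery", and "All examinations shall be conducted on the same day".
- **Tertiary endpoint.** Changes in anthropometric, laboratory and imaging indicators are observed over the same visits, and "these differences will assess the influence of bariatric surgery on these indicators". MRI-PDFF is not mentioned by name.

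**The concern.** The secondary endpoint asks one set of QUS changes to do two jobs. A significant change is to count in favour of QUS, and the trend is to show what surgery did to liver fat. The second use presupposes that QUS measures liver fat, which is what the primary endpoint is there to find out. The first use needs the change in fat to be known from another source, and the endpoint names none.

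If QUS tracks fat poorly, the trend misdescribes the change after surgery. If it tracks fat well, the result is still less precise than the one from MRI-PDFF, and it comes in attenuation or scatter units, not as a liver-fat percentage.

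The Discussion also concedes that subcutaneous fat in people with higher BMI may affect QUS readings. The Introduction says that patients lose a substantial amount of weight after this operation. It is therefore reasonable to expect that disturbing factor to change along with the treatment.

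**Working it through.** The plan gives no figure on this point to reproduce. Its only planned number is the sample size (75, raised to 100), and the point does not depend on it. The main check sets the sections side by side.

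**1. Instrument, role and timing**

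| | QUS (TAI, TSI) | MRI-PDFF |
|---|---|---|
| Role in the primary endpoint | test being judged | gold standard |
| Visits | baseline, months 1, 3, 6, 12 (five) | the same five |
| Timing within a visit | same day | same day |
| Where change after surgery is read | secondary endpoint, named | tertiary endpoint, within imaging, not named |

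The same-day rule is taken to apply at every visit. On that reading each QUS value has a paired reference value, so nothing about data availability requires liver fat to be inferred from QUS.

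**2. Illustration of the precision lost, AC-TAI**

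Assume that QUS, rescaled to fat units, equals MRI-PDFF plus independent noise. For within-patient change, r² is then var(change in PDFF) / var(change in QUS). The variance of a mean change is var/n, so equal precision needs n(QUS)/n(PDFF) = 1/r².

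- Printed pilot value (Results, Table 1): adjusted r = 0.632, n = 21. 0.632² = 0.399 and 1/0.399 = 2.5.
- With the adjustment undone (one predictor): R² = 1 − (1 − 0.399) × 20/21-type correction, that is × (n − 2)/(n − 1) = 19/20, giving 1 − 0.601 × 0.95 = 0.429. So r = 0.655 and 1/0.429 = 2.3. The 0.655 is back-calculated and is not printed in the protocol.
- Range: Fisher's z for 0.632 is 0.745, with half-width 1.96/√18 = 0.462. This gives r from 0.28 to 0.84, and 1/r² from about 13 down to about 1.4.

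**3. SC-TSI**

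No usable factor can be given from the pilot, because Table 1 disagrees with itself. P = 0.982 with n = 21 implies r of about 0.005. The printed adjusted R of 0.229 gives R² = 1 − (1 − 0.052) × 0.95 = 0.10, so r of about 0.32 and a factor of about 10. Among those with PDFF of at least 10% the printed value is 0.677, giving 1/0.458 = 2.2. The external study of MAFLD patients cited in the Discussion has r = 0.727, giving 1/0.529 = 1.9.

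**4. What the factors leave out**

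They describe noise, not bias. They also carry a cross-sectional correlation over to change. The pilot participants had suspected NAFLD and a mean BMI of 26.43, below the trial's entry threshold of 27.5, and no before-and-after change is reported for them. On bias, with 75 completers, a two-sided 0.05 paired t-test and an assumed power of 80%, the detectable mean change is about 0.33 SD of the differences. A modest QUS shift from a cause other than liver fat could therefore reach significance.

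**The case against.** The study is about QUS, and a secondary endpoint that describes QUS change is natural in it. The sentence on surgery is a closing addition that fixes no estimand or test. The tertiary endpoint covers imaging changes at the same visits, and MRI-PDFF is one of the scheduled imaging examinations. The primary endpoint judges QUS against MRI-PDFF before and after surgery, so a failure of QUS should come to light there. No error rate is allocated between the tiers, so moving MRI-PDFF change up one tier alters no test.

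Most of this stands, and it limits the point to what is named and concluded. A reader might infer that MRI-PDFF change is never analysed. The documents do not support that, because the tertiary imaging changes plausibly include it. A reader might also infer that QUS prevails when the two methods disagree. No section states such a rule, and the order of endpoints ranks questions, not which instrument is believed. The protocol's own labels for MRI-PDFF point the other way.

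What does not fall is the sentence itself. The protocol states both the instrument and the inference about surgery, so this is not a detail left to an analysis plan. Even a favourable primary result would not make QUS a better measure of liver fat than the reference it was judged against.

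**Conclusion.** The point holds in a limited form. The secondary endpoint reads the influence of surgery on steatosis from TAI and TSI while their validity is still under examination, although the reference standard is measured at the same five visits. MRI-PDFF change is probably analysed at the tertiary level, but it is unnamed and is not made the measure of the effect on liver fat.

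This conclusion comes from comparing the sections and needs none of the efficiency factors. Those are illustrative only: about 2.3 to 2.5 for AC-TAI, with a range of roughly 1.4 to 13, assuming independent noise and a correlation that carries over to change. They do not show that the QUS trend would be inadequate, since the protocol states no target precision for the change after surgery.

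The stronger reading, that the hierarchy gives QUS priority on disagreement, is not part of the point.

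**What to change.** In the Secondary endpoint section, and in its summary under O (outcome or objective):

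1. State that the effect of surgery on hepatic steatosis is estimated by the within-patient change in MRI-PDFF from baseline to 1, 3, 6 and 12 months, in percentage points with a 95% CI.
2. Report the changes in AC-TAI and SC-TSI beside it, as the test under evaluation. Showing how closely they follow the change in MRI-PDFF would serve the feasibility aim better than a significant QUS change alone.
3. State that no conclusion about surgery's effect on liver fat is drawn from QUS alone.
4. Name MRI-PDFF among the imaging indicators in the Tertiary endpoint section, or refer from there to the secondary endpoint.

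The cost is wording and a little analysis. All the MRI-PDFF examinations are already scheduled, so no scan, visit or patient is added.
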